# Study design and procedures

## Overall study design

This trial is a non-blinded, multicenter, prospective randomized PHASE II clinical trial of enzalutamide treatment to decrease the comorbidity in patients with Corona virus disease 2019 (COVID-19). The trial will be conducted in three phases: explorative phase is to identify any unexpected serious effect of enzalutamide treatment in this novel diagnosis. The second phase (prolongation) will be conducted to receive outcome data to be able to conduct power calculation for the last third phase (full trial). See more details below.

## Treatment arms

Arm (1) (experimental arm):

• Enzalutamide 160mg once daily (4x40mg tablets) + Standard of care

Arm (2) (control arm):

• Standard of care

[figure not shown]

## Treatment duration

The treatment with enzalutamide will start at randomization once daily in the hospital. Patients randomized to the experimental arm will receive the investigational product for the 5 days.

## Rationale for the choice of the patient cohort

If the hypothesis is true, the most benefit would be at the time of highest virus replication in the lung cells. Due to the problem of longitudinal and multiple testing from the lower respiratory tract, it is not fully known when this phase occurs. In the phase of intensive care, the virus replication may be less prominent and it may be too late to get an effect from reducing TMPRSS2 by enzalutamide. The inclusion will therefore be for patients with confirmed COVID-19 infection having mild to severe symptoms with no need of mechanical ventilation but that may be in need of extra oxygen.

In Sweden the majority of patients have symptoms upon testing. Most patients will have mild course of the disease and will not be in need of treatment. Risk of having worsening symptoms has been shown to be in association with higher age and/or other risk factors, such as obesity, heart disease, increased number of other diagnoses. We have therefore set an age limit of at least 50 years. In frail patients, any effects on the respiratory function may be fatale but the most benefit of reducing the virus efficacy may be for patients with several other diagnoses. To balance this, we have chosen to include patients with an estimated expected survival prior to COVID-19 infection of 1 year.

Another consideration of the age limit is to exclude patients with low risk of needing intensive care and/or risk of death. Further the age limit is chosen also due to the effect on enzalutamide on hormonal effects including unknow risk in fertility and teratogenicity.

### Explorative phase:

During the first phase (explorative) 45 patients will be included. Extended testing to identify changes in virus load will be performed to identify any differences between the arms and between gender. This phase is further important to identify any serious adverse event related to enzalutamide treatment in COVID-19 patients.

During this phase the DSMB will have a weekly report from the statistician and give a report to the steering group.

If safety and possible positive effect of enzalutamide for COVID-19 from the first phase may be beneficial and if the DSMB approve to move the trial into the prolongation phase. If needed the inclusion criteria may change to include only one gender or other changes in discussion with DSMB and steering group. Any changes to the protocol will be sent in as amendment to the Swedish Medical Products Agency (MPA) and ethical committee before the inclusion can go beyond 45 patients.

### Prolongation phase:

During the second phase (prolongation) 100 patients will be included. The only change in the trial from the explorative phase is fewer blood samples will be tested at day 2 and 4.

If safety and possible positive effect of enzalutamide for COVID-19 from the prolongation phase may be beneficial the DSMB can move the trial into the full trial. Before start of the full trial a power calculation will be performed for primary end points to identify the size of the population needed to be included. In the interim analysis Cox regression will be adopted and the sample size estimate will be based on simulations. Before initiation into the next phase, inclusion criteria may change to include only one gender or other changes in discussion with DSMB and steering group. Any changes to the protocol will be sent in as amendment to the MPA and ethical committee before the inclusion can go beyond 100 patients.

### Full trial:

The trial will continue as in the prolongation phase if not otherwise decided and approved by the DSMB, Steering group, MPA and ethical committee.

## Procedures and flow chart

## Biological sampling procedures

### Handling, storage, and destruction of biological samples

Blood samples with a total volume of 10 ml to analyze Hb, LPK, Differential leukocyte count, Creatinine, CRP, ASAT, ALAT, ALP, D-dimer, IL-6 will be collected at days 0, 2, 4 and 6. Blood samples to analyze testosterone and estradiol levels will be collected at day 0 and at 6 months. Samples will be analyzed by the accredited central hospital laboratory at each site and will be destroyed immediately after analysis.
In addition, blood samples with a total volume of 15 ml for biobanking will be collected at day 0, day 6 and at 6 months. If discharged before day 6, biobanking will be performed at the day of discharge.
Five ml blood samples for analysis of Covid-19 serological immunity will be collected at 6 months and analyzed by the clinical microbiology laboratory in Umeå University Hospital, Karolinska Institute or Sahlgrenska University Hospital.

Upper respiratory swab will be collected for PCR based SARS-CoV-2 measurement at days 0, 2, 4 and 6. PCR analysis will be performed by the accredited laboratory at each site or at a central study laboratory. Residual material will be biobanked.

### Total volume of blood per subject

The total volume of blood taken from each subject during the study is maximum *100* ml.

### Biobank

Samples taken for biobanking in this study are initially handled by each site but are registered in a biobank at Biobanken Norr (no 472) and handled according to the current biobank laws and regulations. The samples are coded/pseudonymized to protect the subject´s identification. All samples and the identification/code list are stored securely and separately to prevent unauthorized persons from having access to them.

## End of Study

The study ends when the last subject has completed the last follow-up at 6 months. The study may be prematurely terminated if it appears that the treatment involved a large number of serious adverse events (SAE) or if recruitment of subjects cannot be met within reasonable time limits. If the study is prematurely terminated or suspended, the investigator should immediately inform the subjects about this and ensure appropriate treatment and follow-up. The regulatory authority should be informed as soon as possible, but no later than within 15 days.

Decisions on premature termination are taken by the sponsor.

# Subject selection

## Inclusion criteria

To be included in the study, subjects must meet the following criteria:

- - Positive COVID-19 test
  - Mild to severe symptoms of COVID-19
  - Recent hospitalization for COVID-19 symptoms (0-3 days)
  - WHO performance status 0-3
  - Age above or equal to 50 years
  - Can understand all the requirements of the study, provide informed consent, and provide authorization of use and disclosure of personal health information.
  - Estimated expected survival of 1 year (excluding symptoms due to COVID-19)
  - Women of Childbearing Capacity (WOCBC) must:

a) Comply to use of highly effective contraception methods from start of the trial until three months after the last dose of study medication. Acceptable methods according to CTFG guidelines are combined hormonal contraception (oral, dermal, intravaginal), progesterone-only hormonal contraception associated with inhibition of ovulation (oral, injectable, implantable), an intrauterine device, an intrauterine hormone-releasing system or by refraining from heterosexual intercourse during the entire period of risk.
Women of Childbearing Capacity (WOCBC) must:

b) Have a negative pregnancy test

- Male patients

a) Male patients included in the study that have fertile female partners must use adequate contraception within their relationship from start of the trial until three months after the last dose of study medication.

## Definition of COVID-19 positive test

Any clinically used test for COVID-19 disease is accepted.

## Evaluation of Severity of COVID-19 disease

### Mild

No need for extra oxygen.

### Moderate

Need of oxygen but no need of help with respiration.

No need of extra oxygen supply but saturation below 94%.

### Severe

Need of extra help with respiration.

Or No need of extra help with respiration but with saturation less than 90 with additional oxygen.

## Evaluation of comorbidity at day 0

## Other diagnoses are listed in the day 0 form. Medical treatments for any conditions are listed in the day 0 form.

## Evaluation of other risk factors at day 0

Other relevant risk factors will be evaluated in the day 0 form, including:

- Body mass index
- Smoking habits
- Gender
- Age

## Exclusion criteria

## Subjects must not be included in the study if any of the following criteria are met:

- - Severe allergy to enzalutamide
  - Pregnant or Breast-feeding women
  - Need of immediate mechanical ventilation
  - Current hormonal therapy for prostate and breast cancer (finasteride or dutasteride is allowed)
  - Treatment for HIV
  - Treatment with warfarin or Clopidogrel
  - Treatment with immunosuppressive agents. Allowed exceptions are: equivalent medication to prednisolone 10 mg/day or low dose methotrexate 15 mg/week. Any treatment initiated as standard of care for COVID-19 is allowed.
  - Severe immunosuppressive disease
  - Other serious illness or medical condition
  - Current symptomatic unstable cardiovascular disease
  - Stroke in medical history
  - Epileptic seizure in medical history

## Screening

Subject eligibility (that subjects fulfill all inclusion criteria and do not meet any exclusion criteria) is established before inclusion, treatment, or randomization. An eligibility form will be used prior to randomization in the eCRF.

## Withdrawal criteria

Subjects can discontinue their participation in the study at any time without any consequence to his/her continued treatment. The investigator/sponsor can at any time terminate the study for a subject due to, e.g., unacceptable adverse events/adverse reactions or because the subject does not follow procedures in the study protocol. If the subject discontinues the study, follow-up of this subject will be performed according to the clinic’s routine.

# Study treatments

## Description of investigational product(s)

The investigational product is enzalutamide (Xtandi^®^, manufacturer Astellas Pharma Ab), 40 mg film-coated tablets. The patients are treated for five consecutive days, 4 tablets once a day each day, during the hospitalization period. The control group is treated with standard of care.

The investigational product is provided by the manufacturer Astellas Pharma Ab. The investigational product is ordered from the hospital pharmacy according to the clinic´s normal routines and taken from the clinic´s shelf. If changes take place between wards, local routines will be adopted.

## Dose and administration

The defined dose for men in prostate cancer will be used. This means 4 film-coated tablets of 40mg each, once daily, taken orally. See also (<https://www.fass.se/LIF/product?userType=0&nplId=20160310000078>)

## Packaging, labeling, and handling of investigational products(s)

The investigational product is an approved medicinal product (Xtandi^®^) in Sweden. The package currently marketed in Sweden, 4x28 film-coated tablets in blister, is used in the trial. Xtandi^®^ is ordered from the hospital pharmacy according to the clinic´s normal routines and stored in the clinic´s shelf according to the clinic´s normal routines. No additional labelling for clinical trial is used. Discharged patients or patients transferred to ICU will not continue with enzalutamide treatment.

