## Treatment after study end

The treatment period with investigational product in this trial is 5 days or until discharge from the hospital or need of mechanical ventilation, whichever occurs first. After day 7 there is no restriction of medical treatments or inclusion in studies for any experimental therapies. If the patient is stopping treatment of enzalutamide earlier due to any cause, there are not restrictions for after treatments.

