# Methods for measurement of endpoints for clinical efficacy and safety

## Methods for measurement of endpoints for clinical efficacy

### Primary endpoint (variable)

The ordinal scale used to evaluate the primary end-point is used in other trials for COVID-19. It is based on the level of oxygen need if hospitalized and if not hospitalized if the patient has any symptoms or are without symptoms. (See below)

If the patient is at the hospital the 7-point ordinal scale form will be filled. If not hospitalized the follow up will be by phone and registered directly in the eCRF by study personal.

Clinical status as assessed by the 7-point ordinal scale up to 30 days after inclusion:

1) Not hospitalized, no limitations on activities. D

2) Not hospitalized, limitation on activities;

3) Hospitalized, not requiring supplemental oxygen;

4) Hospitalized, requiring supplemental oxygen;

5) Hospitalized, on non-invasive ventilation or high flow oxygen devices;

6) Hospitalized, on invasive mechanical ventilation or extracorporeal membrane oxygenation (ECMO);

7) Death;

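### Section 7.3 ends enzalutamide at ICU transfer and section 7.8 at need of mechanical ventilation, so the two give opposite instructions for an ICU patient who is not ventilated

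*Protocol*

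**What the plan says.** Two places in the protocol state when enzalutamide ends before the planned five days are complete.

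- Section 7.3, on packaging, labelling and handling: "Discharged patients or patients transferred to ICU will not continue with enzalutamide treatment". The triggers are discharge and a change of location.
- Section 7.8, on treatment after study end: the treatment period is "5 days or until discharge from the hospital or need of mechanical ventilation, whichever occurs first". The triggers are completion, discharge and a clinical state. ICU transfer is not among them.

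Section 7.8 also ties other treatment to the stop date. Restrictions end after day 7 in any case, but "If the patient is stopping treatment of enzalutamide earlier due to any cause, there are not restrictions for after treatments".

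Two further places give the planned duration without stopping conditions. Under Treatment duration: "Patients randomized to the experimental arm will receive the investigational product for the 5 days". In section 7.1: "The patients are treated for five consecutive days, 4 tablets once a day each day, during the hospitalization period". Section 7.1 then adds, on moves within the hospital: "If changes take place between wards, local routines will be adopted".

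**The concern.** Both stopping statements name discharge, but they differ on the other trigger. One uses where the patient is; the other uses what support the patient needs. If those two can come apart, some patients have no course of dosing that satisfies both sections.

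Three things depend on the answer.

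- **Exposure.** Need of mechanical ventilation or death is one of the two primary endpoints. Under section 7.8 dosing can run up to the ventilation event. Under section 7.3 it can end before it, in a patient who is already deteriorating. Centres that follow different sections could give different exposure to similar patients.
- **Compliance and the per-protocol set.** Section 7.4 records compliance, and section 10.1 builds the per-protocol set on absence of major deviations and on treatment according to the protocol. A dose given in ICU to an unventilated patient follows section 7.8 and departs from section 7.3; a dose withheld does the reverse.
- **Other therapies.** Early stopping lifts the limits on later treatment, so the date on which experimental therapies become open to the patient moves with the stopping rule applied.

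**Working it through.** The protocol gives no figure on this point and no arithmetic applies. The check is to apply both sections to each type of patient who is within the five days and not discharged.

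1. **In ICU, not needing mechanical ventilation.** Section 7.3 stops; section 7.8 continues. Direct conflict.
2. **In ICU, needing mechanical ventilation.** Both stop.
3. **Needing mechanical ventilation, not yet moved to ICU.** Section 7.8 stops; section 7.3 is silent. A gap, but no contradiction.
4. **On the ward, not needing mechanical ventilation.** Neither stops treatment.

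The conflict is confined to case 1, so the question is whether the protocol leaves case 1 possible.

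- Nothing in the protocol equates ICU transfer with need of mechanical ventilation. The text on potential benefits mentions ICU transfer and invasive ventilation separately.
- The 7-point scale in section 8.1.1 has a category "5) Hospitalized, on non-invasive ventilation or high flow oxygen devices", separate from level 6, which is invasive ventilation or ECMO. The scale does not mention ICU, so no level settles where the patient is treated.
- Such patients are foreseeable. The severe category, which is eligible, includes patients who need extra help with respiration, while the exclusion criteria bar only an immediate need of mechanical ventilation.

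How wide case 1 is depends on a term that section 7.8 leaves undefined.

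- If mechanical ventilation there means invasive ventilation only, case 1 covers ICU patients on high-flow oxygen and those on non-invasive ventilation.
- If it includes non-invasive ventilation, those patients move to case 2. ICU patients on high-flow oxygen alone, or with less support, remain in case 1.

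Case 1 is therefore not empty under either meaning.

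**The case against.** The strongest reply is that the two sections can be read together. Section 7.3 is a specific instruction about ICU patients. Section 7.8 never says that they continue; it is merely silent. A site that applies every stopping condition it finds gets one answer. The protocol also treats intensive care and mechanical ventilation loosely as one stage: the rationale for the patient cohort moves from the intensive-care phase straight to including patients who do not need mechanical ventilation. On this view there is one intended stop point in two wordings.

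That may well explain how the text arose, but it does not settle it. Section 7.8 defines the treatment period by a closed list with a first-to-occur rule, and a site that reads only that section has no reason to look for another trigger. Neither rule sits under Treatment duration or under dose and administration, so finding only one of them is easy. Leaving ward changes to local routines supplies no common reading.

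Other parts of the reply do stand, and they limit the point.

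- A reader might infer a three-way contradiction that includes Treatment duration. That section, like section 7.1, states a planned duration; giving the stopping conditions elsewhere is ordinary drafting.
- A reader might infer that the primary comparison is compromised. The documents do not support this. The intention-to-treat set is all randomized subjects, randomization is stratified by centre, and both primary Cox models adjust for site.
- The per-protocol definition already has a separate fault, since it asks for at least 8 cycles in a five-day treatment. The stopping conflict is therefore not its only obstacle, and membership is in any case decided at the clean file meeting.
- The effect on co-treatment is short. Limits end after day 7 regardless, and section 7.6 permits medication needed for the patient's safety and well-being. What can differ is a few days' access to experimental therapies.

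**Conclusion.** The inconsistency between sections 7.3 and 7.8 is real. For an undischarged patient within the five days who is in ICU and does not need mechanical ventilation, the two sections cannot both be followed. This rests on reading section 7.8 as a complete list, which its wording invites, and on the absence of any statement that ICU transfer and mechanical ventilation are the same event.

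The consequences are possible rather than certain: dosing could differ between centres, the same record could be classed either way for compliance and the per-protocol set, and the release of limits on other experimental therapies could differ in time up to day 7. Intention-to-treat membership does not change.

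No count can be given. A reader might infer that dozens of patients are affected: with the ceiling of 600 at 2:1, arm 1 has 600 × 2/3 = 400 patients, and an assumed 5–15% would be 20–60. The documents give no such rate and leave the full size undetermined. With the 45 patients of the explorative phase, arm 1 has 30, and the same assumption gives 1.5–4.5. The conflict depends on neither figure.

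**What to change.** The sponsor and investigators should:

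- reconcile sections 7.3 and 7.8 into one stopping condition, stated once, with Treatment duration referring to it;
- say whether mechanical ventilation in that condition includes non-invasive ventilation;
- use the same condition for the compliance record and for the per-protocol definition.

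Which condition is right is a clinical decision and is not judged here. The cost is a clarification of protocol wording and a note to sites. Whether it counts as a substantial change under section 13 is for the sponsor to judge.

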## Drug accountability and treatment compliance

Drug accountability will be registered everyday (day 0-4), and treatment compliance will be registered in the CRF.

## Concomitant medications

Medications that are considered necessary for the safety and well-being of the subject can be given at the discretion of the investigator, unless otherwise specified as an exclusion criterion. Concomitant medications should be reported in the Case Report Form (CRF), with exception for on demand medication by topical administration.

Concomitant medication with omeprazole will need adjustment to have the clinical effect. We recommend doubling the dose. If azithromycin is indicated we recommend change to similar antibiotic.

## Destruction

Drugs not used will be disposed at the pharmacy or at the hospital for further disposal according to local regulations.

## Treatment after study end

The treatment period with investigational product in this trial is 5 days or until discharge from the hospital or need of mechanical ventilation, whichever occurs first. After day 7 there is no restriction of medical treatments or inclusion in studies for any experimental therapies. If the patient is stopping treatment of enzalutamide earlier due to any cause, there are not restrictions for after treatments.

# Methods for measurement of endpoints for clinical efficacy and safety

## Methods for measurement of endpoints for clinical efficacy

### Primary endpoint (variable)

The ordinal scale used to evaluate the primary end-point is used in other trials for COVID-19. It is based on the level of oxygen need if hospitalized and if not hospitalized if the patient has any symptoms or are without symptoms. (See below)

If the patient is at the hospital the 7-point ordinal scale form will be filled. If not hospitalized the follow up will be by phone and registered directly in the eCRF by study personal.

Clinical status as assessed by the 7-point ordinal scale up to 30 days after inclusion:

1) Not hospitalized, no limitations on activities. D

2) Not hospitalized, limitation on activities;

3) Hospitalized, not requiring supplemental oxygen;

4) Hospitalized, requiring supplemental oxygen;

5) Hospitalized, on non-invasive ventilation or high flow oxygen devices;

6) Hospitalized, on invasive mechanical ventilation or extracorporeal membrane oxygenation (ECMO);

7) Death;

